### Secondary endpoint

Secondary endpoints are major adverse cardiovascular events, including cardiovascular mortality, myocardial infarction, stroke, sustained atrial tachycardia, or ventricular tachycardia.

### Sample size

Regarding the results from clinical trials in heart failure patients, the incidence of cardiac death or heart failure readmission within 12 months is 15–30% with guideline-directed medical therapy. The patients with DCM enrolled in this study have recovered cardiac function and ejection fraction, and TRED-HF study showed a primary endpoint event rate of 0% in such patients with medication doses unchanged in 6 months. Thus, in this study, it is estimated that the primary endpoint rate in control group and in withdraw group is 5 and 7% over 12 months of follow-up. It is estimated that 218 patients would provide the trial with 80% power to show the non-inferiority of halved doses to original doses, a two-sided alpha of 0.05 and a non-inferiority margin of 10% is applied. Considering a loss to follow up rate of 10%, the final sample size is 240. According to the suggestion of the ethical committee, the current study is a pilot study and 50 patients are intended to be included initially, 25 patients per group. After the initial analysis, more patients might be recruited in a further stage of the study.

### Statistical analysis

Studies will be analyzed using intention-to-treatment and included all patients randomized, regardless of treatment received. Continuous data are expressed as mean ± SD or interquartile range (IQR 25–75). Categorical variables are expressed as a percentage. Continuous variables are compared by an independent sample *t*-test or rank-sum test. The chi-square or Fisher's exact test is used in the analysis of categorical variables. The Cox proportional hazards model was used to analyze and compare the differences in the occurrence of primary endpoint events and key secondary endpoint events within 12 months of follow-up between the trial group and the control group, and the hazard ratio (HR) and 95 % confidence interval will be calculated.

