## Abstract

**Methods:**

An open-label, randomized controlled, prospective study will be conducted among eligible patients with recDCM. During the pilot study phase, we will recruit 50 patients. The primary endpoint is hospitalization for heart failure or heart failure relapse within 12 months. Secondary endpoint is major adverse cardiovascular events, including cardiovascular mortality, myocardial infarction, stroke, sustained atrial tachycardia, or ventricular tachycardia. The results will be analyzed using intention-to-treatment analysis.

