**Figure 1 F1:**
[figure not shown]
Study flow diagram.

In the withdraw group, the doses of ACEI/ARB/ARNI will be reduced by 50% firstly. The symptoms and signs will be assessed in the following 1 month. The echocardiography and NT-proBNP will be performed to see if they could tolerate a further dose reduction of beta-blockers. Then, the dose of beta-blockers will also be reduced by 50% if the cardiac function of participants is stable. The other drugs of the participants will keep unchanged during the follow-up. In the control group, ACEI/ARB/ARNI, beta-blockers, spironolactone, SGLT2-i, and other drugs will be taken with original doses during the follow up.

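### Non-inferiority rests on intention-to-treat as the only named analysis set, with no check on possible non-adherence, and the planned conclusion describes full halving although the arm follows a conditional step-down

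*Protocol article*

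**What the plan says.** The aim is non-inferiority. The Background and rationale frames the hypothesis that way, the Discussion words its hoped-for conclusion that way, and the Sample size section plans for it: "It is estimated that 218 patients would provide the trial with 80% power to show the non-inferiority of halved doses to original doses", with "a two-sided alpha of 0.05 and a non-inferiority margin of 10% is applied". The assumed rates are stated as "the primary endpoint rate in control group and in withdraw group is 5 and 7% over 12 months of follow-up".

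The analysis set is stated twice. The Abstract has "The results will be analyzed using intention-to-treatment analysis", and the Statistical analysis section has "Studies will be analyzed using intention-to-treatment and included all patients randomized, regardless of treatment received". No per-protocol or adherence-based analysis is named in either place.

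The Intervention section reduces ACEI/ARB/ARNI first in the withdraw (half-dose) arm. After a one-month assessment, "the dose of beta-blockers will also be reduced by 50% if the cardiac function of participants is stable". Controls stay on their original doses. The Discussion's intended conclusion concerns halving the ACEI/ARB/ARNI and beta-blocker combination as a whole.

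The present stage is a pilot: "50 patients are intended to be included initially, 25 patients per group". Further recruitment is described as possible after an initial analysis.

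**The concern.** In a superiority trial, non-adherence usually shrinks the difference and works against the claim. In a non-inferiority trial the same shrinkage works for it. This trial is open-label, lasts 12 months, and starts both arms on the same drugs. A half-dose patient who never reduces or who returns to the earlier dose, or a control whose dose is lowered, makes the arms more alike. With intention-to-treat as the only analysis, a reader cannot tell a regimen that is truly non-inferior from one that was not taken.

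A second, distinct point is what the result would be about. Because the second reduction depends on stability, some half-dose patients may never take both halved drugs, and they will have followed the protocol exactly. The randomised comparison is therefore of a step-down strategy. A conclusion about halving both classes would go beyond it.

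**Working it through.** **1. The plan's own figure.** Inputs from the Sample size section: 5% (control), 7% (half-dose), margin 10%, power 80%. The margin is read as 10 percentage points. The distance to the margin is 0.10 − (0.07 − 0.05) = 0.08, and the variance sum is 0.05×0.95 + 0.07×0.93 = 0.0475 + 0.0651 = 0.1126.

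n per arm = (z₁₋α + z₀.₈₀)² × 0.1126 / 0.08²

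- One-sided 0.05: (1.645 + 0.842)² × 17.59 = 108.8, so 109 per arm and 218 in total. This matches the plan.
- One-sided 0.025 (the bound of a two-sided 95% interval): (1.960 + 0.842)² × 17.59 = 138.1, so 139 per arm and 278 in total. This does not match.

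The match supports reading the margin as an absolute difference. That 218 fits one-sided 0.05 and not the stated two-sided 0.05 is a separate matter; here it means only that both levels should be shown.

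**2. Effect of dilution under intention-to-treat.** Assumptions not in the documents: the true rates with full adherence sit on the margin (5% v 15%), and a share c of the half-dose arm carries the control risk. Then

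- half-dose rate p_t = 0.05 + 0.10 × (1 − c)
- SE = √[(0.05×0.95 + p_t(1 − p_t)) / n]
- P(declare non-inferiority) = Φ[(0.10 − (p_t − 0.05)) / SE − z₁₋α]

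Example, c = 20%, n = 109: p_t = 0.13; SE = √[(0.0475 + 0.1131)/109] = 0.0384; 0.02/0.0384 − 1.96 = −1.44; Φ = 7.5%.

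| c | p_t | 109 per arm, one-sided 0.025 | 109 per arm, one-sided 0.05 | 25 per arm, one-sided 0.025 |
|---|---|---|---|---|
| 0 | 15% | 2.5% | 5.0% | 2.5% |
| 10% | 14% | 4.4% | 8.2% | 3.3% |
| 20% | 13% | 7.5% | 13.1% | 4.4% |
| 30% | 12% | 12.3% | 19.9% | 5.7% |

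These are normal approximations. Exact binomial enumeration of the same rule at one-sided 0.025 gives 3.3%, 5.6%, 9.2% and 14.5% at 109 per arm, and 5.0%, 6.3%, 7.9% and 9.9% at 25 per arm. The direction is the same, and the pilot column above is rough.

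**3. What the pilot can decide.** At the planned rates with 25 per arm, SE = √(0.1126/25) = 0.0671. Power is Φ(0.08/0.0671 − 1.96) = 22% at one-sided 0.025, or about 32% at one-sided 0.05. The pilot can hardly declare non-inferiority.

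**4. Strategy against conclusion.** The Intervention section makes the beta-blocker reduction conditional on stability; the Discussion's conclusion carries no such condition. This mismatch needs no assumption about adherence.

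**The case against.** The strongest case against has five parts.

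- **It is an omission.** The article does not say intention-to-treat is the sole analysis, and a supportive set is often left to a fuller document that is not shown. This stands in part: such a document may name one. But the article does not merely stay silent. It commits twice to intention-to-treat whatever was taken, for a question where that choice alone is weak.
- **Crossover is not documented.** This stands. A reader might infer that switching between arms is a feature of the design. No section describes it: controls keep their original doses, and no rule returns half-dose patients to theirs. Non-adherence is a plausible risk of an open-label design, no more.
- **The conditional step is not an intention-to-treat defect.** This stands. A reader might count patients held at step 1 as dilution, but they are adherent to the assigned strategy and a per-protocol set would keep them. Some may also already meet a relapse criterion and so count as half-dose events. The overlap is incomplete, because the article does not tie stability to those criteria: an LVEF fall that stays at or above 50% is not a relapse on the first criterion, yet might hold back step 2.
- **The error rates do not describe this trial.** This stands. The share c is assumed, and full control risk is implausible for patients who stopped at step 1. The current stage has 25 per arm, and the planned analysis is a Cox hazard ratio with no margin on that scale.
- **Per-protocol can bias the same way.** This stands. Dropping half-dose patients who resume because they are worsening removes high-risk patients and may favour non-inferiority. The fix must deal with this.

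**Conclusion.** The point holds in limited form. For a non-inferiority aim, intention-to-treat is the only analysis set named, so nothing in the article guards against possible non-adherence narrowing the contrast. If 10% to 30% of the half-dose arm carried control risk, the false non-inferiority rate at 109 per arm would be 4.4% to 12.3% instead of 2.5% (8.2% to 19.9% instead of 5.0% at the level that reproduces 218). These figures illustrate direction and scale. They assume true rates on the margin, a risk-difference test and a share the documents do not give. The pilot effect is smaller, so the matter bears mainly on a further stage, though the supportive analysis is best fixed before pilot data are seen.

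The documents do not support reading this as intention-to-treat being wrong, or as an error rate actually inflated by these amounts. The mismatch between a conditional step-down and a conclusion about full halving of both classes holds on the text alone. The change should be made, but nothing here invalidates the trial.

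**What to change.** - Keep intention-to-treat and add a per-protocol analysis of the primary endpoint. Claim non-inferiority only if both agree.
- Define per-protocol by adherence to the assigned strategy. Patients held at step 1 by the stability rule count as adherent. Those who never started the reduction, and controls whose dose was lowered, do not.
- Do not simply drop patients who resumed the original dose because of worsening. Keep them in, or count them as events in a sensitivity analysis. State the rule in advance and record the reason for each dose change.
- Report the share of the half-dose arm that reached both halved doses.
- Word the conclusion as being about the step-down strategy, so that the Intervention and Discussion sections agree.

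The cost is one extra analysis, provided the doses actually taken are recorded during follow-up. The per-protocol set loses some patients and some of the balance given by randomisation, which is why it accompanies intention-to-treat and does not replace it.

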### Randomization

The enrolled patients will be randomly assigned into two groups. The randomization list will be automatically generated by the computer system. Before the start of the trial, the randomization list will be configured into the interactive network response system (IWRS, Jinling Rat mini-apps, Nanjing Jihu Network Technology Co., Ltd, Jiangsu, China), and IWRS will assign random numbers to these finally screened patients. Finally, the patients will be randomly assigned to either the withdraw group or control group with a ratio of 1:1 using IWRS.

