### Primary endpoint

The patients will be followed up for 12 months. The primary endpoint is hospitalization for heart failure or heart failure relapse. Heart failure relapse is defined if one of the following criteria is met: (1) LVEF reduction≥10% with LVEF <50%; (2) LVEDVi increased by more than 10%, and exceeded the normal values; (3) 2-fold elevation of NT-proBNP and more than 400 pg/ml; (4) Clinical evidence of heart failure (judged by symptoms, signs and supplementary examination).

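### With about 3 primary events expected in the 50-patient pilot, the standard Cox hazard ratio and Wald interval would be unusable in roughly two of five outcomes

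*Protocol article*

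**What the plan says.** The Statistical analysis section of the protocol article states: "The Cox proportional hazards model was used to analyze and compare the differences in the occurrence of primary endpoint events and key secondary endpoint events". It adds that "the hazard ratio (HR) and 95 % confidence interval will be calculated". The same section allows chi-square or Fisher's exact tests for categorical variables in general, but it attaches no effect estimate or interval to them.

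The Sample size section gives the planning rates: "it is estimated that the primary endpoint rate in control group and in withdraw group is 5 and 7% over 12 months of follow-up". It sets the size of the present study: "50 patients are intended to be included initially, 25 patients per group". It gives no separate event rate or event count for the pilot. It says that more patients might be recruited after the initial analysis. The Primary endpoint section sets the horizon: "The patients will be followed up for 12 months".

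**The concern.** The Cox plan looks as if it was written for the full trial of 218 patients and carried unchanged into a pilot of 50. A Cox model with a single treatment indicator has a finite maximum partial-likelihood estimate only if both arms have at least one event. If one arm is empty, the likelihood is monotone: the estimated hazard ratio runs to 0 or to infinity, and the Wald interval around it means nothing. If both arms are empty, there is nothing to fit.

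The pilot result feeds a decision. The Sample size section makes further recruitment follow the initial analysis, and the Discussion makes further research depend on what this study shows. If the only planned effect estimate fails, either an extreme software value is reported or a replacement is chosen after open-label data have been seen.

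**Working it through.** **Inputs.** From Sample size: 5% (control) and 7% (halved dose) over 12 months, 25 patients per arm, 10% loss, a 10% margin, and 218 patients for the full trial. From Primary endpoint: 12 months of follow-up. From Statistical analysis: Cox hazard ratio with 95% interval.

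**1. Reproducing the plan's own figure.** Treat the margin as an absolute risk difference with unpooled variance:

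n per arm = (z₁₋α + z₀.₈₀)² × [0.05 × 0.95 + 0.07 × 0.93] / (0.10 − 0.02)² = (1.645 + 0.842)² × 0.1126 / 0.0064 = 108.8, so 109 per arm and 218 in total.

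This matches the stated 218 and shows that the 10% margin works on the risk-difference scale. (The match needs a one-sided 0.05, whereas the text says two-sided 0.05. That is a separate matter and does not affect this point.)

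**2. Expected events in the pilot.** 25 × 0.05 = 1.25 and 25 × 0.07 = 1.75, total 3.0.

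**3. Chance of an empty arm, no loss.**
- No control event: 0.95²⁵ = 0.277
- No halved-dose event: 0.93²⁵ = 0.163
- Both empty: 0.277 × 0.163 = 0.045
- At least one empty: 0.277 + 0.163 − 0.045 = 0.395 (simulation: 0.394)
- Exactly one empty: 0.395 − 0.045 = 0.350

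**4. With 10% loss.** If losses are spread over the year, simulation gives 0.42 (about 2.85 expected events). If lost patients contribute nothing (22.5 effective per arm), the chance is 0.315 + 0.195 − 0.062 = 0.449 from unrounded terms (2.7 expected events).

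**5. Sensitivity to the rates (assumed values, 25 per arm, no loss).**

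| Control / halved dose | At least one arm empty |
|---|---|
| 3% / 5% | 61% |
| 5% / 5% | 48% |
| 5% / 7% (plan) | 39.5% |
| 10% / 12% | 11% |
| 15% / 17% | 3% |

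At the plan's rates with 109 per arm, the chance is 0.4%.

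**6. When both arms have events.** A split of 1 versus 2 gives a hazard ratio of about 2.0, with standard error √(1/1 + 1/2) = 1.225 on the log scale. The Wald interval is 2.0 × exp(±1.96 × 1.225), about 0.18 to 22.

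**7. Secondary events.** The article gives no rate. At an assumed 2% per arm, 0.98²⁵ = 0.603, so at least one arm is empty with probability 2 × 0.603 − 0.364 = 0.84, and both with probability 0.36. This is illustrative only.

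**8. Behaviour of the alternatives.**
- *Firth-penalised Cox.* In 4,000 simulated pilots (true hazard ratio 1.41, 10% loss), the estimate and profile interval were finite whenever there was at least one event. Coverage was 97.8%, and the mean log hazard ratio was 0.28 against a true 0.35.
- *Newcombe interval for the risk difference.* This exists even with no events. For 0/25 in each arm, the Wilson upper limit is 1.96² / (25 + 1.96²) = 3.84 / 28.84 = 0.133, so the interval runs from −13.3 to +13.3 percentage points.

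**The case against.** **The text does not say ordinary or Wald.** A Firth fit is still a Cox model that yields a hazard ratio and an interval, and such detail is often left to an analysis plan that is not shown. This stands as far as a missing zero-event rule is concerned; its absence alone would be no finding. But the article itself states the model, the arm size and the rates, and these fit badly together when the model is fitted in the standard way.

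**A reader might infer that in 40% of pilots no hazard ratio or interval exists at all.** The article does not support that. The 40% applies to the maximum partial-likelihood estimate with a Wald interval. In about 35 of those 40 percentage points one arm still has events, and a profile-likelihood interval would have one finite limit. Only the 4.5% with no events carry no information on the ratio.

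**A reader might also infer that an empty control arm is likely,** since "TRED-HF study showed a primary endpoint event rate of 0% in such patients with medication doses unchanged in 6 months". At the plan's own 5% the chance is 28%. The section has already used the 0% figure in arriving at 5%, so adding it again would count it twice.

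**The rates may be higher.** The relapse definition is broad: any one of four criteria suffices. The sensitivity table shows the problem shrinking at higher rates and growing at lower ones. The direction is unknown, and the plan should work at its own planning rates.

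**Fisher's exact test handles empty cells, and the Discussion admits the small sample.** Both are true, so a between-arm test would not have to be invented. But the test supplies no planned effect estimate or interval, and the general admission of small size is not linked to the Cox analysis.

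**Conclusion.** The point holds for the pilot. On the article's own rates and arm size, about 3 primary events are expected. There is about a 40% chance (42 to 45% with 10% loss) that the only named effect estimate, fitted in the standard way, is 0, infinite or undefined with an unusable Wald interval. This rests on the 5% and 7% rates applying to the pilot, on independent patients, and on a treatment-only model with a 12-month horizon. Over the assumed rates examined it ranges from 3% to 61%. The 40% concerns the primary endpoint only; no rate is given for secondary events.

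The flaw is worth correcting before analysis, but it does not invalidate the trial. It is a matter of which estimate is planned at this event count. It does not show that the pilot data would be uninformative, nor that Cox regression is unsuitable at full size.

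**What to change.** In the Statistical analysis section, for the pilot:

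- Make the main estimate for the primary endpoint the 12-month risk in each arm with an exact (Clopper-Pearson) 95% interval, plus the risk difference with a score-type 95% interval (Miettinen-Nurminen or Newcombe, named in advance). These can be computed with zero events and are on the scale on which the 10% margin reproduces 218.
- Report any hazard ratio, for primary or secondary events, as supportive only, from Firth-penalised Cox regression with a profile penalised-likelihood 95% interval.
- State that no hazard ratio is given when neither arm has an event.

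The cost is a few sentences, with no extra patients, visits or data. Three downsides should be accepted openly. The intervals remain wide: even with no events in either arm, the Newcombe limit of +13.3 points lies beyond the 10% margin. Firth penalisation shrinks the log hazard ratio by about 20% at this event count ((0.35 − 0.28) / 0.35). A fixed-time risk also needs a stated rule for patients lost before month 12, about 5 of 50 at the planned 10% loss.

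### Non-inferiority is sized on a 10-point risk difference, but the only analysis named for the primary endpoint is a Cox hazard ratio with no margin

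*Protocol article*

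**What the plan says.** All of the following is in the protocol article.

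- **Aim.** Background and rationale states the hypothesis as non-inferiority of the halved doses. The Discussion expects that the comparison may lead to a non-inferiority conclusion.
- **Sample size.** The assumption is that "the primary endpoint rate in control group and in withdraw group is 5 and 7% over 12 months of follow-up". With "a two-sided alpha of 0.05", "218 patients would provide the trial with 80% power", and "a non-inferiority margin of 10% is applied". The scale of the 10% is not named. The same section limits the present stage to 50 patients, 25 per group, on the ethics committee's suggestion, with possible further recruitment after an initial analysis.
- **Statistical analysis.** For the primary endpoint: "The Cox proportional hazards model was used to analyze and compare the differences in the occurrence of primary endpoint events", with a hazard ratio and 95% CI. Chi-square or Fisher's test is mentioned only in general terms: "exact test is used in the analysis of categorical variables". No sentence links any interval to the 10% margin.

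**The concern.** A non-inferiority trial is decided by comparing a confidence limit with a margin on the same scale. Here the margin belongs to a difference in 12-month risks and the reported effect is a hazard ratio. Without a hazard-ratio margin or a conversion rule, a reader holding the hazard ratio and its interval cannot say whether the margin has been met. An analysis aimed at differences can return a significant difference or none, and the absence of a significant difference is not evidence of non-inferiority. At stake is whether the conclusion foreseen in the Discussion has a decision rule behind it, in the pilot or in any enlarged trial.

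**Working it through.** **Inputs.** From Sample size: 12-month risks of 5% (control) and 7% (halved dose), margin 10%, power 80%, alpha 0.05 stated as two-sided, 218 patients in total, pilot of 25 per arm. From Randomization: 1:1 allocation.

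**1. Reproducing 218 and finding the scale of the margin.** For a risk difference with unpooled variance,

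n per arm = (z_alpha + z_power)² × [0.05×0.95 + 0.07×0.93] / (0.10 − 0.02)²

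The bracket is 0.0475 + 0.0651 = 0.1126, and 0.1126/0.0064 = 17.594.

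| One-sided alpha | Matching interval | z sum, squared | n per arm | Total |
|---|---|---|---|---|
| 0.05 | 90% CI | (1.645 + 0.842)² = 6.183 | 108.8, so 109 | **218** |
| 0.025 | 95% CI | (1.960 + 0.842)² = 7.849 | 138.1, so 139 | 278 |

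The stated 218 is matched exactly by a 10-point absolute margin at one-sided 0.05. A relative margin of 1.10 is ruled out, because the assumed ratio 7/5 = 1.40 already lies beyond it.

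**2. What the margin becomes on the hazard-ratio scale.** Under proportional hazards, HR = ln(1 − p_control − 0.10) / ln(1 − p_control).

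| Control 12-month risk | Calculation | Equivalent HR |
|---|---|---|
| 2% | ln 0.88 / ln 0.98 | 6.33 |
| 5% | ln 0.85 / ln 0.95 | 3.17 |
| 10% | ln 0.80 / ln 0.90 | 2.12 |

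The same 10 points therefore correspond to very different hazard ratios, so the conversion cannot be left to the reader.

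**3. Testing on the Cox scale instead.** At 5% control risk the margin is HR 3.17 and the assumed truth is ln 0.93 / ln 0.95 = 1.41. Events needed for 80% power at one-sided 0.025 are 4 × 7.849 / [ln(3.17/1.41)]² = 31.4/0.650 = 48.3, so 49. At a mean risk of 6% that is about 805 to 817 patients. With 218 patients about 13 events are expected (218 × 0.06), and power is about 31%. The planned size does not carry over to the Cox scale.

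**4. Whether the hazard ratio can be estimated in the pilot.** Expected events are 25 × 0.05 = 1.25 and 25 × 0.07 = 1.75.

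P(at least one arm has no events) = 1 − (1 − 0.95^25)(1 − 0.93^25) = 1 − 0.7226 × 0.8370 = 0.395.

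In those trials the estimated hazard ratio is zero, infinite or undefined, and the usual interval around it fails.

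**5. What a risk-difference rule would deliver.**
- With 109 per arm, SE = √(0.1126/109) = 0.0321 and 0.08/0.0321 = 2.489. Power with a 95% CI is Φ(2.489 − 1.960) = 70.2%; with a 90% CI it is Φ(2.489 − 1.645) = 80.1%.
- With 25 per arm, SE = 0.0671 and 0.08/0.0671 = 1.192. Approximate power is 22.1% (95% CI) or 32.5% (90% CI).
- With 0/25 against 0/25, the Newcombe upper limit is z²/(25 + z²). At 95% this is 3.841/28.841 = 13.3 points, above the margin. At 90% it is 2.706/27.706 = 9.8 points, only just below it, and this outcome has probability 0.2774 × 0.1630 = 4.5% under the assumed risks.

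**The case against.** The strongest reply has four parts.

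*A journal article condenses, and the interval method and decision rule may be in an analysis plan that is not shown.* This stands for the details. It does not remove the point, because the article itself fixes both the margin and a primary effect measure on another scale. For the same reason, the criticism is limited to what is written in this article.

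*The word absolute never appears.* Correct. The scale is inferred, but from an exact match to 218 and from the impossibility of a 1.10 ratio.

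*This is a disclosed pilot.* Also correct: the small size is named as a limitation, and the 39.5% in step 4 comes from having 25 per arm, so it would shrink in the full trial. The scale mismatch does not depend on size, and the Discussion does not reserve the non-inferiority conclusion for the later stage.

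*A hazard-ratio interval can serve non-inferiority.* It can, given a stated hazard-ratio margin, but none is stated, and step 3 shows that 218 patients would then be far too few.

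Three stronger readings are tempting and not supported:
- A reader might infer that Fisher's test is a planned primary test and would miss an excess at the margin. The article assigns chi-square and Fisher to categorical variables in general and only Cox to the primary endpoint.
- A reader might infer that a non-significant result will be taken as non-inferiority. The article never says so.
- A reader might infer that the margin accepts the 15% at the low end of the range quoted for heart-failure patients. The margin bounds a difference, so 15% follows only at exactly 5% control risk. The quoted range is also for cardiac death or heart-failure readmission, a different endpoint.

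**Conclusion.** The point holds as a mismatch of scale within the article. The margin is 10 points on the 12-month risk difference, the only named primary analysis is a Cox hazard ratio without a margin or conversion, and a non-inferiority conclusion is nevertheless foreseen. The equivalent hazard ratio is 3.17 at the assumed 5% control risk and ranges from 6.33 to 2.12 for control risks of 2% to 10%, assuming proportional hazards. In the pilot, under the article's own 5% and 7%, there is a 39.5% chance that no usable hazard ratio exists.

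A linked inconsistency must be settled with it: 218 corresponds to one-sided 0.05, whereas the stated two-sided 0.05 and the planned 95% CI leave about 70% power at that size. The power figures rest on the normal approximation and on the assumed risks.

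**What to change.** 1. Make the 12-month risk difference, half-dose minus control, the primary estimate. Use a score-based interval (Miettinen-Nurminen or Newcombe), or a Kaplan-Meier risk difference if there is censoring.
2. State that the margin is 10 absolute percentage points and that non-inferiority is judged only by the upper confidence limit against it. Keep the Cox hazard ratio and its CI as descriptive.
3. Reconcile interval and size. Either declare one-sided 0.05 with a 90% CI, which 218 supports, or keep two-sided 0.05 with a 95% CI and restate the power of 218 as about 70%. Holding 80% power with a 95% CI would take 278 before loss to follow-up.
4. For the 50-patient stage, report the risk difference and CI as estimation only, and state that no non-inferiority verdict will be drawn. Even an event-free pilot has a Newcombe 95% upper limit of 13.3 points. Align the Discussion with this.

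**Cost.** No new data are needed in the pilot. The price is a less favourable stated power, or a larger full trial, or an openly declared 90% interval, and the loss of any confirmatory claim from the pilot.

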**Discussion:**

The study will provide important evidence of whether it is safe and effective to halve the dosage of neurohumoral blockades in recDCM patients.

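### The Cox hazard ratio named for MACE will often not be estimable with 25 patients per arm, and the pilot MACE result is not labelled descriptive

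*Protocol article*

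**What the plan says.** The Secondary endpoint section defines a single composite: "Secondary endpoints are major adverse cardiovascular events, including cardiovascular mortality, myocardial infarction, stroke, sustained atrial tachycardia, or ventricular tachycardia". The Statistical analysis section names a Cox proportional hazards model to "analyze and compare the differences in the occurrence of primary endpoint events and key secondary endpoint events within 12 months of follow-up", reported as a hazard ratio with 95% confidence interval. As MACE is the only secondary endpoint listed, it is what the key secondary events refer to.

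The Discussion paragraph of the Abstract says that the study will give evidence of "whether it is safe and effective to halve the dosage of neurohumoral blockades in recDCM patients". The end of the Background and the opening of the main Discussion state the safety aim in similar terms.

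The Sample size section says that "50 patients are intended to be included initially, 25 patients per group", with more patients possible after an initial analysis. Its error rate and margin ("a two-sided alpha of 0.05 and a non-inferiority margin of 10% is applied") belong to the primary endpoint. No event rate, margin or largest tolerable hazard ratio is given for MACE.

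The same Statistical analysis section also provides percentages and chi-square or Fisher's exact tests for categorical variables. The main Discussion names the small sample as a limitation.

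**The concern.** Cardiovascular death, myocardial infarction, stroke and sustained arrhythmia are named as endpoints only within MACE. The between-group statistic fixed for them is a relative measure that needs events in both arms. In 50 patients with recovered function, followed for a year, there may be few or none. With an empty arm the Cox estimate runs to zero or infinity and has no usable Wald interval. With both arms empty it does not exist.

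When the hazard ratio can be computed, its interval will be very wide and the article gives no limit to hold it against. The risk is that the pilot reports either no MACE estimate or an uninformative one, and that nothing in the article tells the reader how little this says about safety. It matters because further recruitment is to be considered after the pilot is analysed.

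**Working it through.** **Inputs from the article.** 25 per arm (Sample size), 1:1 allocation (Randomization), 12 months of follow-up (Primary endpoint), two-sided 0.05, and primary-endpoint risks of 5% (original dose) and 7% (half dose).

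**Assumption.** The article gives no MACE rate, so control risks of 1% to 10% over 12 months are used. Losses are ignored in the binomial calculations.

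**The plan's own figure.** The only powered quantity is 218 patients for the primary endpoint. Per arm, n = (z_α + z_β)² × [0.05×0.95 + 0.07×0.93] / (0.10 − 0.02)².
- One-sided 0.05: (1.645 + 0.842)² × 0.1126 / 0.0064 = 108.8, so 109 per arm, 218 in total. This matches.
- One-sided 0.025, which the stated two-sided 0.05 implies: 138.1, so 139 per arm, 278 in total. This does not match. It is a separate matter and nothing below rests on it.

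There is no corresponding figure for MACE.

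**Step 1: chance that the hazard ratio has no finite estimate.** With q = (1 − p)^25 per arm, P(at least one arm empty) = q₀ + q₁ − q₀q₁, and P(both empty) = q₀q₁.

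| Risk in both arms | q | At least one arm empty | Both empty |
|---|---|---|---|
| 1% | 0.778 | 95% | 61% |
| 2% | 0.603 | 84% | 36% |
| 5% | 0.277 | 48% | 8% |
| 10% | 0.072 | 14% | 0.5% |

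If the true hazard ratio is 3, the chance of an empty arm at these control risks is 88%, 69%, 29% and 7%.

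For scale, borrow the article's own primary-endpoint risks of 5% and 7%: 0.277 + 0.163 − 0.045 = 0.395. So the Cox model has a 40% chance of an empty arm even at those rates, with 25 × 0.12 = 3 events expected in all.

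**Step 2: power to detect harm, 25 per arm, two-sided 0.05.** Fisher by exact enumeration; log-rank by simulation (exponential times, 3,000 runs).

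| True risks, original vs half dose | Fisher | Log-rank |
|---|---|---|
| 2% vs 6% | 0.2% | 4% |
| 2% vs 10% | 2.3% | 17% |
| 5% vs 15% | 7.2% | 21% |

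Fisher's test needs 6 events against 0: p = 2 × C(25,5)/C(50,5) = 0.0502 for 5 vs 0, and 0.022 for 6 vs 0. By Schoenfeld's formula, 80% power for a hazard ratio of 3 needs 4 × (1.96 + 0.842)² / (ln 3)², or 27 events. The expected number at that hazard ratio is about 1.0, 2.0, 4.8 and 9.3 at control risks of 1%, 2%, 5% and 10%.

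**Step 3: what the data could still allow.**
- 0/25 in an arm: exact two-sided 95% upper limit = 1 − 0.025^(1/25) = 13.7%.
- 0/25 vs 0/25: the Wilson upper limit is 3.84/(25 + 3.84) = 0.133, so the Newcombe interval for the risk difference is −13.3 to +13.3 points. It exists where the hazard ratio does not.
- 3 events, roughly evenly split: the 95% interval for the hazard ratio spans a factor of exp(1.96 × √(4/3)) = 9.6 either way.

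**The case against.** Much of the case on the other side stands.

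- **No rule equates non-significance with safety.** A reader might infer that halving would be called safe if the MACE hazard ratio were not significant. No section says so. The conclusion that the main Discussion foresees is non-inferiority in maintaining cardiac function, which is the primary-endpoint question and has a stated margin.
- **Safety is wider than MACE.** Heart failure hospitalization and relapse are the primary endpoint, and other adverse events are recorded at follow-up.
- **An upper limit is planned.** The hazard ratio comes with a 95% interval, so an upper limit will be reported whenever the ratio can be estimated. What is absent is a stated harm limit to compare it with.
- **Non-estimability depends on an assumed rate.** At 10% it is 14%, or 7% with a hazard ratio of 3. The composite includes sustained atrial tachycardia, so a very low rate is not established.
- **A null result is not certain whatever the truth.** At a control risk of 5%, Fisher's test reaches 80% power when the half-dose risk is about 39%.
- **The stage is openly a pilot.** Its size follows the ethics committee's advice, and the small sample is acknowledged.

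Two further replies carry less weight. Fisher's exact test is available when an arm is empty, but it gives a p-value of very low power and no interval. It is also true that an article may leave zero-event handling to the full protocol or analysis plan. Here, however, the article itself names the Cox hazard ratio, and the point is that this choice suits the pilot badly.

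**Conclusion.** The point holds in a limited form. For MACE the article names a statistic that, at 25 per arm, has no finite value in 48% to 95% of trials if the 12-month risk is 1% to 5% in both arms, and in 14% if it is 10%. When it can be computed, a non-significant result would do little to exclude a tripling of risk. The MACE risks are assumptions, and the conclusion weakens as they rise. The 40% figure at 5% and 7% uses the article's own rates, but those belong to the primary endpoint.

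The documents do not support the stronger charge that the trial plans to declare halving safe because a MACE comparison is not significant. The fault is a poorly suited summary statistic, together with no statement that the pilot MACE result is descriptive. Acknowledging a small sample in general does not supply that statement.

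**What to change.** 1. **Statistical analysis section, 50-patient stage.** Make the main MACE summary the number of patients with an event per arm with exact (Clopper-Pearson) 95% intervals, and the 12-month risk difference, half dose minus original dose, with a Newcombe or score 95% interval. Both exist with zero events.
2. **Losses.** These intervals do not handle censoring and the article expects 10% loss to follow-up. State how patients lost before 12 months are counted, for example with a sensitivity analysis.
3. **Hazard ratio.** Keep it as supportive only, from a Firth-penalised Cox model with profile-likelihood interval, when at least one event occurs.
4. **Abstract and main Discussion.** State that the pilot MACE result is descriptive, that it is reported by the upper limit of the risk-difference interval, and that absence of a significant difference is not evidence of safety.

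The cost is a few sentences, with no new patients or data. The downside is that the intervals will be visibly wide and the pilot cannot support a safety conclusion on MACE.
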